## Abstract

**Background:**

Axial spondyloarthritis (axSpA) is a disabling inflammatory joint disease with chronic low back pain (CLBP) as leading symptom. Recognizing axSpA in the large amount of CLBP patients is difficult for general practioners (GP). This evaluation aims to assess the effect of a referral strategy for axSpA in young primary care patients with CLBP by comparing the use of the strategy with usual care. The effect is measured at three different levels; by patient reported outcomes (the clinical effect), process and costs evaluation.

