**Methods/Design:**

This study design is a cluster randomized controlled trial with GP as clusters. GPs throughout the Netherlands are invited to participate and randomized to either the intervention or the control group. Patients from participating GPs are invited to participate if they have ever been registered with low back pain, without radiation (ICPC L03) and aged 18–45 years. To be included in the study, patients need to have current low back pain and chronic low back pain (>12 weeks). In the intervention arm a referral strategy for axSpA will be applied in CLBP patients, in the control arm care as usual will be provided for CLBP patients. The referral strategy consists of four easy to use variables. All are questions about the back pain complaints of the patients. Data is prospectively collected in an online database at baseline (T0), 4 months (T1), 12 months (T2) and 24 months (T3). After time point T1 (4 months) patients from the control group will also receive the intervention i.e. the application of a referral strategy for axSpA. The effect of the referral strategy is measured at three different levels, by patient outcomes (e.g. pain scores, quality of life), process measures (e.g. number of axSpA diagnoses by rheumatologists) and by costs (work productivity and health care resources use). Our primary outcome is the Roland Morris Disability Questionnaire after 4 months, secondary outcomes are pain and quality of life. Costs will be assessed before and after the use of the referral strategy, to estimate if the use of the strategy will lead to a reduction in health care costs and improvement in work participation.

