**Discussion:**

It is anticipated that using the axSpA referral strategy for primary care CLBP patients will increase the quality of life of CLBP patients, will result in more (correct) diagnoses of axSpA by the rheumatologists, and will be cost-effective. Ultimately, the results of this study may contribute to the startup of a national implementation of the axSpA referral strategy to identify timely CLBP patients with axSpA.

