### Objective of the evaluation

This study entails a clinical effect, process and cost evaluation of using the axSpA referral strategy for primary care CLBP patients. The study aims to determine to what extent use of the rule, in comparison with usual care, leads to less disability and pain and improved quality of life in CLBP patients. Second, it evaluates if the referral strategy leads to more diagnosis of axSpA and finally health care costs and work participation will be compared before and after the application of the referral strategy.

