### Data analysis

Effects at 4 months and the process evaluation will be analysed according to the intention-to-treat principle. The baseline characteristics of the patients will be summarized by randomisation group, reported as mean (standard deviation) or median (interquartile range) for continuous variables and count (percent) for categorical variables.

As this is a cluster-randomized trial mixed effect regression analysis will be used to compare the mean RMDQ score after four months between the intervention and usual care group. Fixed effects include allocation group and result of the referral strategy (referral y/n). As the effect of the referral strategy is expected in the subgroup of patient with a referral advice, an interaction term between allocation group and result of the referral strategy will also be included. A random intercept will be included adjusting for clustering [24, 25]. This random intercept stand for the effect of different primary care practices (i.e. clusters).

For the secondary outcomes we will again use a mixed effect regression analysis to estimate the effect of the use of the referral strategy after 4 months on process level (i.e. the number of axSpA diagnoses by a rheumatologists), pain (VAS pain), quality of life (SF-36 version 2 and EQ-5D) and disease activity (BASDAI). We will use linear regression for continuous outcomes and logistic regression for dichotomous outcomes. Similar to the primary outcome analysis an interaction term and random intercept will be used to take into account interaction between allocation group and referral strategy and clustering. We intended to assess the effect of using the referral strategy also at 12 and 24 months. However, patients in the control group receive also an advice based on the referral rule after 4 months. Contract between the intervention and control group is no longer present. Therefore, individual trajectories will be modeled using random effect regression with patient outcome as the dependent variable and time as covariate and a random intercept for patient.

For the cost evaluation we will compare costs before and after the application of the referral strategy. We will consider costs of provided health care and costs due to loss of work-productivity. In order to calculate costs, the volume of care will be linked to the actual, integrated cost prices per medical service [26].

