## Discussion

This evaluation aims to assess the effects on patient outcomes, processes and costs of a referral strategy for axSpA in young primary care patients with CLBP by comparing the use of the strategy with usual care. The study started in July 2014 and the first results are expected in May 2016.

There are only a very few impact studies in the field of prognostic research. In a recent review there were 61 development studies and only 2 (3 %) of them also had an impact evaluation [27], an essential step to asses clinical effectiveness and costs.

The main strength of this study is that it provides information on the process outcome (referral to the rheumatologists and result of the diagnostic process) and on the patient outcomes (pain and quality of life). The combination of process and patients outcomes allows for a better interpretation of findings. An effect in process does not necessarily results in improved patient outcomes. Possible absence of effect in patient outcomes, on the other hand, may be the result of insufficient improvement in the process. Further, the study measures the impact of a validated referral strategy. The referral strategy has already shown to discriminating axSpA patients from other CLBP patients [4]. We have chosen to only test the impact of the CaFaSpA referral strategy as this is the cheapest and the most feasible strategy for primary care of all proposed referral strategies for axSpA.

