A weakness of the study is that the contrast between intervention and control groups disappears after 4 months, as patients of the control group are also provided with the advice of the referral strategy. Nevertheless our primary outcome is assessed before the contract between intervention and control group is eliminated. We expect that 4 months is a sufficient period to achieve a substantial improvement in the primary outcome by using the referral strategy in the intervention group. For other outcomes we can use a before after design within patients which is acceptable as the back pain complaints are chronic. Another potential weakness is that patients are selected by a registry, rather than only actively care seeking patients are invited to participate. This can lead to a lower participation rate of the invited patients and a potential selection bias of only severe cases of low back pain. However in the prior CaFaSpA studies, the same approach to select participants by the GP register was conducted and this didn’t result in a more severe low back pain study population [4, 5]. In both CaFaSpA studies was the VAS pain comparable with other low back pain cohorts. One last limitation of this study is that the intervention i.e. the CaFaSpA referral rule is applied by research assistant not by GPs themselves, this pragmatic approach can influence the outcomes of the study. We have chosen for this pragmatic approach as GPs pointed before the start of study that it is often too busy during consultation hour to properly ask the questions of the referral rule and that the application of the referral rule would not be uniform but heavenly time dependent.

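### Costs are compared only before versus after the strategy, although the aim is a comparison with usual care and a randomised usual-care arm exists up to 4 months

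*Protocol article*

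**What the plan says.** The protocol article states the cost analysis three times, each time as before versus after. The Data analysis section has "For the cost evaluation we will compare costs before and after the application of the referral strategy". The Objective of the evaluation has "finally health care costs and work participation will be compared before and after the application of the referral strategy". The abstract's Methods/Design gives the same comparison a causal purpose: "to estimate if the use of the strategy will lead to a reduction in health care costs and improvement in work participation".

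The overall aim is worded differently. The abstract's Background says the effect is assessed "by comparing the use of the strategy with usual care", at three levels of which costs is one. In the main Discussion the aim reads "costs of a referral strategy for axSpA in young primary care patients with CLBP by comparing the use of the strategy with usual care", with costs again one of the levels. The abstract's Discussion anticipates that the strategy "will result in more (correct) diagnoses of axSpA by the rheumatologists, and will be cost-effective".

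The 4-month between-arm mixed models in Data analysis cover the RMDQ, axSpA diagnoses, pain, quality of life and disease activity. Costs are not listed. Under Control group, usual-care patients and their GPs receive the outcome of the rule only after 4 months. The main Discussion names the later loss of contrast as a weakness and adds "Nevertheless our primary outcome is assessed before the contract between intervention and control group is eliminated". For other outcomes it defends a within-patient before/after design on the ground that the complaints are chronic.

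**The concern.** A comparison with usual care and a before/after comparison answer different questions. The first isolates what the strategy adds. The second measures everything that changed between two periods. Patients must have current low back pain to enter, so some later fall in resource use and work loss may occur without any strategy. Referral may meanwhile add visits early on. Calendar-time changes in care use enter as well. Followed as written, the plan would credit or charge all of this to the strategy.

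The before period also differs between arms. In the intervention arm the rule is completed in the inclusion telephone call and the questionnaires follow, so the before period can only be what the baseline questionnaire looks back on. In the control arm it also includes the 4 months before the advice letter.

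At stake is one of the trial's three declared levels of evaluation, and the cost argument for wider implementation. The primary outcome is not affected.

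**Working it through.** **1. The passages side by side (protocol article).**

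| Place | Comparator for costs |
|---|---|
| Abstract, Background; main Discussion | Usual care |
| Abstract, Methods/Design | Before versus after, to judge whether the strategy lowers costs |
| Objective of the evaluation | Before versus after |
| Data analysis, cost paragraph | Before versus after |
| Data analysis, 4-month between-arm models | Costs not listed |

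The cost analysis matches the specific cost objective. It does not match the overall aim, and it cannot serve the causal purpose given in the abstract.

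**2. What each comparison estimates.** Let τ be the strategy's effect on mean cost and δ the change that would have occurred anyway.
- Before/after in patients given the strategy: τ + δ.
- Between arms from T0 to T1, if δ is common to both arms: (τ + δ) − δ = τ.

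The bias of the first is δ, in whichever direction δ runs. The document gives no cost mean, standard deviation or trend, so δ cannot be computed.

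**3. The plan's own sample-size figures (Sample size section).**
- 180 × 2 = 360, doubled for the 50 % with a positive rule.
- Design effect: 1 + (16 − 1) × 0.05 = 1.75.
- 360 × 1.75 = 630, and 630 / 0.75 = 840 enrolled.

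The chain from 360 to 840 reproduces. A difference of 2.5 with SD 6.0 needs 91 per arm (182 in total), so the 180 works as a two-arm total rather than per group. That is a separate matter and does not affect this point.

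**4. Precision of a 4-month randomised cost comparison.** Assumptions: equal arms, the design effect of 1.75 applied to costs, two-sided α of 0.05, 80 % power and a normal approximation.
- Followed per arm: 630 / 2 = 315.
- Effective per arm: 315 / 1.75 = 180.
- Detectable difference: (1.96 + 0.84) × √(2/180) = 0.30 SD of cost.
- Rule-positive patients only: effective 180 × 0.50 = 90 per arm, so (1.96 + 0.84) × √(2/90) = 0.42 SD.

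The last figure is cautious, because fewer patients per practice would lower the design effect. Without a cost SD, neither can be put in euros.

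**5. Sensitivity of a before/after test to drift (all inputs assumed, for illustration only).** Take τ = 0, drift δ of 0.05 to 0.20 SD, within-patient correlation ρ of 0.3 to 0.7, and no clustering. The standard error is √(2(1 − ρ)/n). With n = 315:
- δ = 0.05, ρ = 0.3: SE = √(1.4/315) = 0.067, and the test is significant in about 12 % of trials.
- δ = 0.20, ρ = 0.7: SE = √(0.6/315) = 0.044, and the test is significant in over 99 % of trials.

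The nominal rate is 5 %. The range shows that a significant before/after result need not reflect the strategy. It does not estimate the bias in this trial.

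**The case against.** The before/after design is disclosed and reasoned. The authors name the lost contrast as a weakness, argue that chronic complaints make within-patient comparison acceptable, and write the cost objective to match. Patients are found by a register search rather than at a consultation, and the authors report that the same approach did not select more severe cases before. Regression to the mean should therefore be weaker than in a trial recruiting at a peak of care use. Four months would also capture early referral costs and largely miss later productivity gains.

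Most of this stands as qualification. The choice is open, not hidden. Regression to the mean may be small, but the requirement of current pain leaves some, and natural course and time trends remain. The short window is a good reason to keep the longer comparison. None of it explains why the randomised contrast goes unused for costs while it exists. The chronicity argument answers the loss of contrast after 4 months, not the period before.

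A reader might infer more than the document supports:
- **That the article claims cost-effectiveness.** It states an expectation in the abstract, not a result or a planned estimand.
- **That the absence of an analysis joining costs to the EQ-5D is a fault.** A condensed article commonly leaves this to the full protocol or analysis plan.
- **That the 4-month contrast would be the only unbiased comparison.** It would be the randomised one, but practices and patients are unblinded, outcomes are self-reported and 25 % loss is assumed.

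**Conclusion.** The point holds in this form: the only cost comparison stated is uncontrolled, while the stated aim and the causal use of the result call for a comparison with usual care, which the trial can make up to 4 months. The bias equals whatever cost change would have happened without the strategy. Neither its size nor its sign can be derived from the document, and any percentage would be an assumption.

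The randomised comparison would be modestly precise: about 0.30 SD detectable in all followed patients and about 0.42 SD in rule-positive patients, if the design effect of 1.75 carries over to costs. Its feasibility rests on the cost questionnaires being included at T1. The Data collection and Outcome measures sections imply this but do not say it. The recall period is not given either.

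This should be corrected, but it concerns a secondary level of evaluation and leaves the primary analysis untouched.

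**What to change.** - Add health-care and productivity costs to the 4-month between-arm analyses: the difference between randomised arms over T0 to T1, adjusted for T0 costs, with practice-level clustering (a practice random intercept, or a bootstrap that resamples practices).
- Base any statement that the strategy changes costs on that comparison.
- Keep the longer before/after comparison, label it uncontrolled, and define its before period for each arm.
- Align the wording of the aim with the cost objective, and limit cost-effectiveness wording to what the two analyses can support.
- Confirm that the cost questionnaires are given at T1 and state the period they cover.

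**Cost.** If the questionnaires are already given at T1, this needs extra analysis and no new data. The price is a short horizon: the randomised result will show early referral costs and may miss later productivity effects, and its interval will be fairly wide.

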## Discussion

This evaluation aims to assess the effects on patient outcomes, processes and costs of a referral strategy for axSpA in young primary care patients with CLBP by comparing the use of the strategy with usual care. The study started in July 2014 and the first results are expected in May 2016.

There are only a very few impact studies in the field of prognostic research. In a recent review there were 61 development studies and only 2 (3 %) of them also had an impact evaluation [27], an essential step to asses clinical effectiveness and costs.

The main strength of this study is that it provides information on the process outcome (referral to the rheumatologists and result of the diagnostic process) and on the patient outcomes (pain and quality of life). The combination of process and patients outcomes allows for a better interpretation of findings. An effect in process does not necessarily results in improved patient outcomes. Possible absence of effect in patient outcomes, on the other hand, may be the result of insufficient improvement in the process. Further, the study measures the impact of a validated referral strategy. The referral strategy has already shown to discriminating axSpA patients from other CLBP patients [4]. We have chosen to only test the impact of the CaFaSpA referral strategy as this is the cheapest and the most feasible strategy for primary care of all proposed referral strategies for axSpA.

A weakness of the study is that the contrast between intervention and control groups disappears after 4 months, as patients of the control group are also provided with the advice of the referral strategy. Nevertheless our primary outcome is assessed before the contract between intervention and control group is eliminated. We expect that 4 months is a sufficient period to achieve a substantial improvement in the primary outcome by using the referral strategy in the intervention group. For other outcomes we can use a before after design within patients which is acceptable as the back pain complaints are chronic. Another potential weakness is that patients are selected by a registry, rather than only actively care seeking patients are invited to participate. This can lead to a lower participation rate of the invited patients and a potential selection bias of only severe cases of low back pain. However in the prior CaFaSpA studies, the same approach to select participants by the GP register was conducted and this didn’t result in a more severe low back pain study population [4, 5]. In both CaFaSpA studies was the VAS pain comparable with other low back pain cohorts. One last limitation of this study is that the intervention i.e. the CaFaSpA referral rule is applied by research assistant not by GPs themselves, this pragmatic approach can influence the outcomes of the study. We have chosen for this pragmatic approach as GPs pointed before the start of study that it is often too busy during consultation hour to properly ask the questions of the referral rule and that the application of the referral rule would not be uniform but heavenly time dependent.

If this study succeeds in demonstrating an impact of applying the referral strategy for axSpA in young CLBP patients, the potential benefit may be substantial. The care provided to CLBP patients can be improved, it will be easier for GPs to refer the CLBP patient with a high risk for axSpA to the rheumatologist. And an earlier diagnosis of axSpA has favorable outcomes, as several studies have shown that an effective treatment in axSpA patients results in a lower disease activity, improved quality of life and enhanced work participation [28, 29]. And finally the gain for society; CLBP is a great socio-economic burden for society. When one of the causes for CLBP is recognized earlier and subsequently diagnosed and treated in an earlier stage this can lead to decreased sick leave due to back pain and increased work productivity.

## Abbreviations

AxSpA, Axial Spondyloarthritis; BASDAI, Bath Ankylosing Spondylitis Disease Activity Index; CaFaSpA, Case Finding Axial Spondyloarthritis; CLBP, Chronic Low Back Pain; EQ-5D, EuroQol five dimensions; GP, general practioner; ICPC, International Classification Primary Care; iMCQ, IMTA Medical Consumption Questionnaire; iPCQ, IMTA Productivity Costs Questionnaire; LBP, low back pain; RMDQ, Roland Morris Disability Questionnaire; SF-36, Short Form Health Survey; VAS, Visual Analogue Scale; YLD, Years Lived with Disability
